### Study outcomes

#### Primary outcomes.

The primary outcomes of the study are

Proportion of individuals screened for CMD and SUD among those seeking care for NCDsProportion of those screened positive who are successfully referred and linked to appropriate mental health or substance use disorder services.Proportion of those linked to care who initiate evidence- based treatment and support.

#### Secondary outcomes.

The secondary outcomes of the study are

Proportion of facilities who started integrating the modelIncremental cost of the implementation of the model

#### Outcome measures.

There shall be two sets of outcome measures: key process outcome measures and intervention outcome measures.

1. **Key process outcome measures**

The process outcome measures shall include the number of stakeholders sensitized to start integrated mental health services; awareness of HCWs about mental health services integration into NCD services at baseline; number of training sessions conducted; number of HCWs trained for mental health services; acceptance of the training offered to HCWs and feasibility of the interventions; and number of health care workers having the knowledge and motivation to implement the model. (Table 6)

2. **Intervention outcome measures**

The intervention outcome measures shall include implementation outcomes, patient/clinical outcome measures, and service outcomes, which are listed in Tables 7–9.

**Table 7 pone.0332359.t007:** Implementation outcome measures.

Implementation Outcome	Level of analysis	Methods	Measurements
**Acceptability** (perception among stakeholders (e.g., consumers, providers, managers, policymakers) that an intervention is agreeable)	Facility and Individual provider Individual consumer	• Qualitative assessments using ID and FGD with Stakeholders using tool that is already developed for the project	• Planned after implementation of each iteration of the model
**Adoption** (intention, initial decision, or action to try to employ a new intervention)	Facility and Individual provider Organization or setting	• Pre-post items to capture adoption of evidence-based practices	• proportion of facilities where HCWs are screening, for MSUD among patients with other NCDs • proportion of ANM and ASHA doing screening and referral and using the Digital App for MSUD among patients with other NCDs • proportion of CHO doing screening, management and referral and using the Digital App for MSUD among patients with other NCDs • proportion of MO doing assessment and management and using the Digital App for MSUD among patients with other NCDs • proportion of ANM and ASHA who have conducted community awareness/ engagement session on MSUD among patients with other NCDs
**Feasibility (Yes/No)** (compatible or actual fit) The extent to which an intervention can be carried out in a particular setting or organization	Facility and Individual providers Organization or setting	• Quantitative assessments from the Healthcare facility registers and government databases.	• Proportion of patients screened for MSUD among those screened/confirmed with NCD (N + M) • Proportion of screened positive/confirmed for MSUD managed, are under follow up, complied with referral
**Fidelity** The degree to which an intervention was implemented as it was designed in an original protocol, plan, or policy	Facility and Individual provider (adherence, quality of delivery, program component differentiation, exposure to the intervention, and participant responsiveness or involvement)	• Quantitative assessments from the Health care facility registers and government databases.	• Proportion of facilities who started integrating the model • The proportion of patients who initiated the treatment, following up with the health facility • The proportion of the patients in whom the continuum of care was ensured.
**Penetration** (integration of a practice within a service setting and its subsystems)	Organization or setting Facility level: The integration of MH screening in NCD within public health system; (the extent to which MH screening, linkages and treatment completed)	• Quantitative assessments from the Health care facility registers and government databases.	• Proportion of NCD patients screened for MSUD ◦ numerator assessed with patients registered in the digital App/ record review ◦ denominator assessed with HWC/PHC/CHC register (patients with NCD registered at the facility) • Among those with a positive MSUD screen ◦ proportion who are screened, managed and referred ◦ numerator assessed with patients registered in the digital App/ record review ◦ denominator assessed with HWC/PHC/CHC register (patients with NCD registered at the facility)
**Sustainability** (extent to which a newly implemented treatment is maintained or institutionalized within a service setting’s ongoing, stable operations)	Administrators Organization or setting (1) passage (a single event such as transition from temporary to permanent funding) (2) cycle or routine (i.e., repetitive reinforcement of the importance of the evidence-based intervention through including it into organizational or community procedures and behaviours, such as the annual budget and evaluation criteria), (3) niche saturation (the extent to which an evidence-based intervention is integrated into all subsystems of an organization)	• Quantitative assessments from the health care facility registers and government databases.	• Proportion of health facilities that continued the service delivery model developed by this study (also note the number of weeks for which the model was used after it was implemented) • Proportion of ANM/ ASHA continuing to screen, and refer for MSUD among patients with other NCDs • Proportion of CHO continuing to screen, manage and refer for MSUD among patients with other NCDs • Proportion of MO continuing to assess, manage and refer for MSUD among patients with other NCDs • Proportion of ANM/ ASHA/ CHO/ MO continuing to use digital App
**Impact** (long term effect of the implementation)	Facility and Individual provider Organization or setting	• Quantitative assessments from the health care facility registers and government databases. • Qualitative assessments from Patient/Service users	• Proportion of facilities offering screening, management and referral services for MSUD among patients with other NCDs • Experience/ satisfaction of HCWs with the delivery of integrated services using IDI at all levels of facilities • Experience/ satisfaction of patients with the integrated services using IDI at all levels of facilities
**Implementation Cost** (direct, indirect, training, logistics)	Organization or setting	Quantitative assessments from the cost involved in delivery of the Interventions from all the Health care facilities	Incremental cost of the implementation of the service delivery model

**Table 8 pone.0332359.t008:** Patient/Clinical Outcome Measures.

1.	Proportion of patients screened by ANM/ASHA for mental disorders and substance use disorders among those seeking care for NCDs
2.	Proportion of screened positive patients by ANM/ASHA for mental disorders and substance use disorders among those seeking care for NCDs that were referred for further evaluation/management
3.	Proportion of patients screened by CHO for mental disorders and substance use disorders among those seeking care for NCDs
4.	Proportion of screened positive patients by CHO for mental disorders and substance use disorders among those seeking care for NCDs that were offer intervention and/ or referred for further evaluation/ management
5.	Proportion of screened positive patients for mental disorders and substance use disorders among seeking care for NCDs that were assessed by MO
6.	Proportion of screened positive patients for mental disorders and substance use disorders among those seeking care for NCDs that were started on treatment by MO
7.	Proportion of patients with MSUD who were back referred to CHO that followed up with CHO
8.	Proportion of those screened positive for mental disorders and substance use disorders assessed and managed (treated and/or referred) and are under follow-up care at 6 and 12 months compared to the baseline.
9.	Number of teleconsultations through DMHP and Tele MANAS utilized.
10.	Proportion of drop outs (patients who do not reach the recommended next referral point).
11.	Number of patients diagnosed with MSUD among patients with other NCDs

**Table 9 pone.0332359.t009:** Service outcome measures.

1. Proportion of PHC that have at least one medicine to treat depressive disorder
2. Proportion of PHC that have at least one medicine to treat anxiety disorder
3. Proportion of PHC that have at least one medicine to treat alcohol use disorder (short term)
4. Proportion of PHC that have at least one medicine to treat alcohol use disorder (long term)
5. Proportion of PHC that have at least one medicine to treat tobacco use disorder
6. Proportion of CHC that have at least one medicine to treat depressive disorder
7. Proportion of CHC that have at least one medicine to treat anxiety disorder
8. Proportion of CHC that have at least one medicine to treat alcohol use disorder (short term)
9. Proportion of CHC that have at least one medicine to treat alcohol use disorder (long term)
10. Proportion of CHC that have at least one medicine to treat tobacco use disorder
11. Does the district hospital have at least one medicine to treat depressive disorder?
12. Does the district hospital have at least one medicine to treat anxiety disorder?
13. Does the district hospital have at least one medicine to treat alcohol use disorder (short term)?
14. Does the district hospital have at least one medicine to treat alcohol use disorder (long-term)?
15. Does the district hospital have at least one medicine to treat tobacco use disorder?
16. Proportion of PHC that have routine blood tests (LFT, KFT)
17. Proportion of CHC that have routine blood tests (LFT, KFT)
18. Does the district hospital have routine blood tests (LFT, KFT)?
19. Proportion of health facilities that have IEC material on MSUD available and displayed
20. Number of mental health awareness sessions held (at facility/in community)

The process of implementation will be evaluated by the COM-B model of the Behavior Change Wheel (BCW) [35]. As per this model, there are 3 key factors & multiple sub-factors capable of changing behavior, namely capability, opportunity, and motivation.

Program learning shall be documented using the qualitative methods (FGD, IDI), including listing barriers and facilitators, reasons for not following through with treatment, follow-up consultations (provider plus beneficiary), feasibility and acceptability of the training module/program through questionnaires and FGDs, technical and logistical challenges in delivering the program, challenges faced by staff during the completion of the course and their subsequent engagement (reaching out and referring), difficulties encountered when participating in the online refresher training, and the overall satisfaction level of staff post-training.

The timeline for all the study-related activities is provided in the Gantt chart (Table 10).

**Table 10 pone.0332359.t010:** Gantt Chart of the ICMR MINDS.

Project Activities		2024		2025		2025		2026		2026		2027	
		**Q 1**	**Q 2**	**Q 3**	**Q 4**	**Q1**	**Q2**	**Q3**	**Q4**	**Q1**	**Q2**	**Q3**	**Q4**
**1.1**	**Ethical clearance**												
**1.2**	**Registration of trial with CTRI**												
**2.1**	**Formative Phase**												
**2.2**	**Implement Initial MD in NCD Integration Model-0 in Block 1.**												
**2.3**	**Implement modified MD in NCD Integration Model-1 in Block 2.**												
**2.4**	**Implement modified MD in NCD Integration Model-X in Block.**												
**2.5**	**Program Learning Activities**												
**3.1**	**Implement the best model of MD in NCD Integration of Model-X in 2/3 new blocks.**												
**3.2**	**Process-monitoring activities**												
**3.3**	**Outcome measurement activities**												
**3.4**	**Development of scale-up plans**												
**3.5**	**Final analysis**												
**3.6**	**Dissemination of results**												

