**b) Mixed Methods Evaluation Using CFIR and IRLM:**

The implementation model (M0) will be evaluated using a combination of qualitative and quantitative methods, guided by the Consolidated Framework for Implementation Research (CFIR) [32] (Table 2) and the Implementation Research Logic Model (IRLM) (Table 3) [33]. These frameworks will help identify the constructs that contribute to or hinder the integration of MSUD services within NCD care across different settings. The IRLM will support mapping the inputs, activities, outputs, and outcomes, while the CFIR constructs will guide data collection on implementation processes and context.

**Table 3 pone.0332359.t003:** Pre-facility, facility, and post-facility components of the logic model and specific aspects of the logic model for the implementation framework.

	Pre-Facility	Facility		Post-facility	
Objectives	Identifying study sites Addressing stigma Human resources	Integrate screening, diagnosis, treatment, and linkage within the health system, monitoring of treatment adherence		Sustainability of screening and treatment for mental health conditions Integrated care being scaled up at the state level	
Activities	Stakeholder’s meetings Community engagement Capacity building workshops	Stakeholder’s meetings Involve policymakers Community engagement Capacity building of relevant HCWs, workshops Creating an online platform for seamless data collection and integration		Identify barriers of sustainability and scaling up Collaboration with policymakers and other stakeholders Budgetary allocation	
Personnel involved	Policymakers, health department, community leaders, HCW	ASHA workers, ANM, CHO, MO Private doctors		Policymakers Health department officials	
Outcomes	Increased public awareness and reduced stigma Availability of trained human resources	At least 70% screening for target mental health conditions among people seeking care for NCD At least 70% of those screened positive, get appropriate treatment and linkage to care. Screening and treatment are acceptable, feasible, adoptable, and affordable		Adoption and scaling up of the integrated care at the state level	

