**Specific aspects of the logic model for the implementation framework**					
**Target population**	**Underlying assumptions**	**Resources and challenges**	**Activities (input)**	**Output**	**Outcomes**
Persons with NCD seeking treatment at the health facilities Beneficiaries Persons with NCD and comorbid target mental illness and tobacco and alcohol misuse	Theoretical assumption of how the program will work? It is possible to train the existing HCWs and integrate screening, treatment, and linkage to higher services	ANMs, CHO, PHC MOs, GPs (private hospitals)	Training and capacity building for existing HCW cadre to deliver the intervention package Establishing a monitoring system Training of a cadre in the existing healthcare system in monitoring Periodic quantitative and qualitative monitoring Advocacy Additional funds and resource allocation	Number of persons with NCD screened, identified with target mental health conditions, treated, and successfully linked at various health care levels	• % screened • % identified with mental health conditions • %treated as per the guideline • % successfully linked with higher services • % retained in the treatment • Generating a cascade of care with a target at least 70% at each level • Acceptability, feasibility, Adoption, fidelity, implementation cost of the program

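### In Table 7, the second Penetration measure is defined among screen-positive patients but is given all registered NCD patients as its denominator

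*Protocol article*

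**What the plan says.** The Penetration row of Table 7 (Protocol article, Outcome measures) holds two measures. The first is the proportion of NCD patients screened for mental and substance use disorders (MSUD). Its numerator comes from the app or record review, and its denominator from the facility's NCD register.

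The second measure is introduced as "Among those with a positive MSUD screen ◦ proportion who are screened, managed and referred". Beneath it stand the same two source lines as for the first measure: "numerator assessed with patients registered in the digital App/ record review" and "denominator assessed with HWC/PHC/CHC register (patients with NCD registered at the facility".

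Elsewhere the protocol measures this step of the cascade among screen-positive patients:

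- **Table 3, facility outcomes:** "At least 70% of those screened positive, get appropriate treatment and linkage to care".
- **Table 3, specific aspects of the logic model:** "Generating a cascade of care with a target at least 70% at each level".
- **Table 7, Feasibility row:** "Proportion of screened positive/confirmed for MSUD managed, are under follow up, complied with referral".
- **Primary outcomes, second item:** referral and linkage among those screened positive.
- **Table 8, items 2, 4, 5, 6 and 8:** referral, intervention, assessment, treatment and follow-up, each among screen-positive patients.

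Nothing in the article corrects the denominator line in the Penetration row.

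**The concern.** A proportion defined among screen-positive patients cannot have every registered NCD patient as its denominator. The likeliest explanation is that the source lines of the first measure were repeated under the second without adjustment.

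The outcome lists and Table 8 do not say where numerators and denominators are to be obtained. The Penetration row does, so a site looking for a working rule for this step may well take it from there. Sites that follow the denominator line and sites that follow the opening words would report different quantities under one name.

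A site that follows the denominator line would also report a figure that mixes how common positive screens are with how well the programme handles them. A district with few positive screens would score lower than one with many, even if both managed the same share of their positives.

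**Working it through.** **Inputs**

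- s, screening coverage among registered NCD patients: 70% (the protocol's target) to 90% (the per-step rate in the Sample size section).
- q, screen-positive rate among those screened: not given for MSUD as a whole. The only comorbidity figure is 9.3–23% for depression (Introduction), used here as a proxy. A rate of 40% is added as an assumption.
- m, share of screen-positive patients managed or referred: 100% for the ceiling; 0.9 × 0.9 = 0.81 at the design's referral and management rates.
- It is assumed that every patient in the numerator is also on the register.

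**The plan's own figures.** The protocol gives no expected value for this measure. Its related figures reproduce: n = 1.96² × 0.70 × 0.30 / 0.10² = 80.67, rounded up to 81 facilities per district; 7 × 81 = 567; 0.9 × 0.9 × 0.9 = 0.729. None of them uses the Penetration denominator.

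**Formulas**

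- Register denominator: value = s × q × m.
- Screen-positive denominator: value = m.

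**Ceiling with the register denominator (m = 1)**

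| Screen-positive rate q | s = 0.70 | s = 0.90 |
|---|---|---|
| 9.3% (depression only) | 0.70 × 0.093 = 6.5% | 0.90 × 0.093 = 8.4% |
| 23% (depression only) | 0.70 × 0.23 = 16.1% | 0.90 × 0.23 = 20.7% |
| 40% (assumed) | 0.70 × 0.40 = 28% | 0.90 × 0.40 = 36% |

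Even at s = 1 and m = 1 the value is q, so it can never exceed the screen-positive rate among registered patients.

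**Same performance, different prevalence.** Take two districts, both with s = 0.9 and m = 0.81.

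- q = 9.3%: 0.9 × 0.093 × 0.81 = 6.8%.
- q = 23%: 0.9 × 0.23 × 0.81 = 16.8%.

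With screen-positive patients as the denominator, both score 81%.

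**How far the ceiling could rise.** Screening also covers anxiety, alcohol and tobacco, so q may be well above the depression figures. If four conditions are treated as independent, three illustrative sets of assumed rates give:

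- 9.3%, 9.3%, 10% and 20%: 1 − 0.907 × 0.907 × 0.90 × 0.80 = 40.8%.
- 23%, 23%, 20% and 30%: 1 − 0.77 × 0.77 × 0.80 × 0.70 = 66.8%.
- 23%, 23%, 30% and 40%: 1 − 0.77 × 0.77 × 0.70 × 0.60 = 75.1%.

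**Positive rate needed for the register version to reach 70%**

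- Perfect screening and management: 0.70 / 1 = 70%.
- The design's 0.9 per step: 0.70 / 0.729 = 96%.
- 70% screening and 70% management: 0.70 / 0.49 = 143%, which is impossible.

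**Numerator.** The numerator is "proportion who are screened, managed and referred". Among screen-positive patients, being screened is automatic, so that word adds nothing. The joining word, read literally, leaves out a patient who was treated without referral. Table 8 item 8 counts patients treated, referred or both.

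**The case against.** **The opening words settle the meaning.** They restrict the measure to screen-positive patients, and many consistent statements elsewhere stand against one faulty line. A careful analyst would probably recover the intended base. That is fair, and it limits the harm. It does not make the row usable as written, because the line names the population to be counted and not merely where to look.

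**It may be deliberate whole-population coverage.** Penetration can reasonably be expressed over all eligible patients. The measure's own opening words contradict that reading here, and the first measure in the row already uses that base.

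**The 70% mark is not in this row.** This stands. A reader might infer that the measure is bound to fail a 70% threshold. The Penetration row sets no threshold; the target belongs to the cascade, and Table 3 ties it to screen-positive patients. The size of any shortfall also depends on a combined screen-positive rate that the protocol does not give and that a high tobacco rate could raise considerably.

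**The screening proportion has several bases.** It is taken over those seeking NCD care (primary outcomes), over registered patients (Penetration), and in the Feasibility row as "Proportion of patients screened for MSUD among those screened/confirmed with NCD (N + M". A reader might call this a further error. Feasibility and Penetration are separately defined constructs, so different bases are not in themselves a contradiction. The article does not say that the register is cumulative or lists people who did not attend. That reading is not supported.

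**Conclusion.** The contradiction is on the face of Table 7 and should be corrected. With the register denominator, the second Penetration measure is capped by the screen-positive rate and varies with prevalence at equal performance. The illustrative ceiling is 6.5–20.7% at the depression-only rates and 28–36% at an assumed 40%, against 100% for the same programme when screen-positive patients are the denominator. These ranges illustrate the effect and do not bound it, because the combined MSUD rate is unknown. The cap and the dependence on prevalence rest only on the formula and on the numerator patients being on the register.

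A reader might infer that the trial's main result is compromised. It is not: the second primary outcome already uses screen-positive patients, Penetration is not a listed secondary outcome, and the sample size does not draw on it. The error is confined to one implementation outcome.

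**What to change.** In the Penetration row of Table 7:

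1. Make the denominator of the second measure the patients with a positive MSUD screen at the facility, counted from the app or record review.
2. Remove the redundant reference to being screened from its numerator, and count patients managed and/or referred, in line with Table 8 item 8.
3. Keep the NCD register as the denominator of the first measure only.

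If managed or referred patients as a share of all registered NCD patients are also of interest, report that as a separate, clearly named measure that is not compared with the 70% target.

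The cost is a wording change, passed on to the sites. No new data collection should be needed: under Intervention components, the app digitises the screening tools and tracks treatment started in screen-positive patients. Data collection is planned to run to October 2026, so the wording should be settled before sites compile this measure.

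### Table 7, Penetration: the measure for screen-positive patients is given the all-NCD-register denominator, so it would track screen positivity and coverage as well as care

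*Protocol article*

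**What the plan says.** Table 7 of the protocol article lists two measures under Penetration. The first is "Proportion of NCD patients screened for MSUD". Its numerator line is "numerator assessed with patients registered in the digital App/ record review" and its denominator line is "denominator assessed with HWC/PHC/CHC register (patients with NCD registered at the facility".

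The second is introduced by "Among those with a positive MSUD screen" and asks for the "proportion who are screened, managed and referred". Beneath it, the same numerator and denominator lines appear again, word for word.

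Elsewhere the document takes screen-positive patients as the base for this step:

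- The second primary outcome is a proportion of screen-positive patients.
- The Feasibility row of Table 7 asks for the "Proportion of screened positive/confirmed for MSUD managed, are under follow up, complied with referral".
- Table 8, items 2, 4, 5, 6 and 8, all start from screen-positive patients.
- Table 3 sets the target "At least 70% of those screened positive, get appropriate treatment and linkage to care", and its second part adds "Generating a cascade of care with a target at least 70% at each level".

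**The concern.** A proportion among screen-positive patients cannot have every registered NCD patient as its denominator. Most of those patients may have screened negative, and some will not have been screened at all. With that denominator, the measure mixes three things: how many were screened, how many screened positive, and how many positives received care. Only the last is what the heading promises.

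Three consequences follow if the row is programmed as printed. A district that manages nearly all its positives would show a low figure. Two districts giving identical care would differ because their positivity differs. The final report could also carry two irreconcilable figures for one step of the cascade, one from this row and one from the primary outcome.

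The wording has two smaller faults. Counting screened patients is redundant among people who are by definition screened. The row also joins management and referral, whereas Table 8 item 8 accepts treatment, referral or both. A patient treated on site without referral would fail the first definition and meet the second.

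**Working it through.** **The plan's own figures.** The document states no expected value for this measure. The nearest figures are in Sample size, and both reproduce:

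- n = 1.96² × 0.70 × 0.30 / 0.10² = 80.67, rounded up to 81 facilities per district.
- Cascade: 0.9 × 0.9 × 0.9 = 0.729.

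Neither uses the Penetration row, and the cascade product contains no positivity term.

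**Definitions.** Let s be the share of registered NCD patients screened, q the share of those screened who are positive, and m the share of positives who meet the care criterion.

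- Value under the heading (screen-positive denominator): m.
- Value under the printed denominator: s × q × m.
- Ceiling under the printed denominator, with perfect care (m = 1): s × q.

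**Inputs.** For s, 0.70 is the Table 3 target, 0.90 the Sample size step rate and 1.00 the maximum. For m, 0.90 is the step rate and 1.00 the maximum. For q the document gives nothing. The Introduction quotes 9.3–23% for depression alone among patients with chronic disease, which is used here as an assumption. Because the screen also covers anxiety, tobacco and alcohol, 40% and 50% are shown as further assumptions.

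| s | q (assumed) | m | Printed denominator, s × q × m | Screen-positive denominator, m |
|---|---|---|---|---|
| 0.70 | 0.093 | 0.90 | 5.9% | 90% |
| 0.90 | 0.093 | 0.90 | 7.5% | 90% |
| 0.90 | 0.23 | 0.90 | 18.6% | 90% |
| 1.00 | 0.23 | 1.00 | 23.0% | 100% |
| 0.90 | 0.40 | 0.90 | 32.4% | 90% |
| 0.90 | 0.50 | 0.90 | 40.5% | 90% |

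Rows two and three have identical screening and care. The printed measure differs by a factor of 0.23 / 0.093 ≈ 2.5 through positivity alone.

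**Positivity needed for the printed measure to read 70%**, q = 0.70 / (s × m):

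- s = m = 1: 0.70.
- s = m = 0.90: 0.70 / 0.81 = 0.864, about 86%.
- s = 0.70, m = 0.90: 0.70 / 0.63 = 1.11, which is impossible.
- s = m = 0.70, both steps exactly on target: 0.70 / 0.49 = 1.43, which is impossible.

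**The case against.** The strongest reply is that this is a copied sub-bullet in one of many implementation measures. The correct base is stated in the primary outcomes, in Table 3, in Table 8 and two rows higher in the same table, so a careful analyst would see what is meant. The 70% target is not attached to this row, and no primary or secondary outcome or sample-size figure uses it. All of that stands and limits the severity. It does not make the line right: the row fixes a denominator explicitly, and that denominator contradicts its own heading.

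Some stronger readings are tempting, but the documents do not support them:

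- A reader might infer that, because the numerator lines are also identical, the two measures must return the same number. The numerator line names a data source, and the indicator line above it says what is counted. Under Intervention components, the app is to track both numbers screened and treatment started in screen positives, so one source can supply both counts.
- A reader might take a particular low range as what the trial will report. Any such range rests on an assumed positivity.
- A reader might think the document consistently defines management as treatment and/or referral. Table 8 item 8 does, but Intervention components describes management as treatment and referral.
- A reader might regard this as the only place where data sources for post-screen care are given. The Feasibility row also names its sources. Penetration is the row that sets out numerator and denominator separately.

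**Conclusion.** Wrong as written, of moderate severity at most. The denominator of the second Penetration measure conflicts with its heading and with the screen-positive base used elsewhere for the same step. That conclusion needs no assumption.

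The size does. As printed, the measure cannot exceed screening coverage × positivity. It would read about 6–23% if positivity were 9.3–23% with 70–100% screened and 90–100% managed, and about 32–41% if positivity were 40–50% with 90% screened and 90% managed. In the 90%-managed cases the intended value is 90%. It could reach 70% only at very high positivity, about 86% when screening and management are both 90%. It should therefore not be judged against the 70% target.

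It would be wrong to infer that the primary outcomes or the 81 facilities per district are compromised. Their wording and arithmetic do not draw on this row.

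**What to change.** For the second Penetration measure:

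- **Denominator:** patients with a positive MSUD screen recorded in the app or records at that facility in the reporting period.
- **Numerator:** those same patients with a recorded management event.
- **Wording:** delete the redundant reference to being screened, and reconcile the joint management-and-referral criterion with Table 8 item 8 so that one definition applies in both places.

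If coverage of the whole NCD population is intended instead, keep the register denominator, drop the restriction to screen-positive patients, and state that the measure is not compared with 70%.

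The cost is a change of table wording and of the matching report definition. The app is already planned to track screening, treatment started in screen positives, and linkage, so no new data are needed. Data collection is expected to run to October 2026, so the correction can be made before the final analysis.
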